### Data management

Investigators are trained to record data promptly, completely, and correctly in the CRFs according to original observation. On-site auditing will be performed at least three times during the study period, with reports and feedbacks provided in written form. Data input will be performed with EpiData software (Version 3.1). Dataset will be locked when the following tasks have been completed: (1) patient recruitment and follow-up are completed, (2) data collection, input and double-checked is performed without errors, and (3) all data queries have been solved. Data management will be performed by Peking University Clinical Research Institute who is independent from the investigators and sponsors.

### Data analysis

#### General principles

All statistical analyses will be performed with SPSS 14.0 software package (SPSS, Chicago, IL, USA) and SAS 9.2 software (SAS Institute, Cary, NC, USA) by statisticians in the Department of Biostatistics of Peking University First Hospital. Since the safety of intervention has been confirmed by our previous pilot study, interim analysis is not planned. Analyses will be performed on an intention-to-treat basis, that all subjects will be analyzed in the group which they were assigned to. For the primary outcome (the incidence of PPCs within 30 days after surgery), per protocol analysis will also be performed.

#### Baseline data

Statistical description will be provided for baseline data such as demographic variables, medical history, preoperative medications, and perioperative management.

#### Outcome analysis

Primary outcome (the incidence of PPCs within 30 days after surgery) will be compared with χ2 test. The difference between groups and the 95% confidence interval of the difference will be calculated.

For secondary outcomes, continuous variables with normal distribution will be analyzed using an unpaired *t* test; continuous variables with abnormal distribution or ranked data will be analyzed using Mann-Whitney *U* test; categorical variables will be analyzed using the chi-squared test, continuity correction chi-squared test or Fisher exact test; time-to-event results will be analyzed using the Kaplan-Meier estimator, and the differences between groups will be tested by the log-rank test. Subgroup analyses will be performed according to the type of the surgery (upper abdominal or thoracic).

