### Randomized, blinding and study drug administration

Random numbers were generated in a 1:1 ratio using the SAS 9.2 software package (SAS Institute, Cary, NC, USA) by a biostatistician. Randomization will be stratified according to the type of surgery (upper abdominal or noncardiac thoracic surgery). Study drugs (penehyclidine hydrochloride 1 mg/1 ml, or water for injection 1 ml) are provided as clear aqueous solution in the same 1 ml ampoules (manufactured by Chengdu List Pharmaceutical Co., Ltd., Sichuan, China) and labeled according to the randomization results by a biostatistician and a pharmacist who are independent of patient recruitment and data collection. The results of randomization are sealed in the envelopes and stored at the site of investigation until the end of the study.

During the study period, consecutively recruited patients will be assigned sequential numbers according to which the study drugs will be dispensed by a study coordinator. Study drugs are administered by inhalation in the night (7 pm) before surgery, in the morning (7 am) of surgery, and then every 12 hours until postoperative day 2, resulting in a total number of 7 inhalations. Study drug inhalation is performed with a jet nebulizer (DNA100, manufactured by Congren Medical Equipment Co., Ltd., Xiamen, China) for extubated patients or a vibrating mash nebulizer (Agrogen Professional Nebulizer System, AG-AP6000CH, Aerogen Ltd, Ireland) for patients with mechanical ventilation. Before inhalation, study drugs (penehyclidine hydrochloride 0.5 mg/0.5 ml for patients in the penehyclidine group, or water for injection 0.5 ml for patients in the placebo group) are diluted with normal saline to 6 ml. The performance of each study drug inhalation is recorded in the CRFs.

Patients, investigators, and healthcare team members are all blinded to the study group assignment throughout the study period. In case of an emergency (such as development of a severe adverse event), attending physicians or surgeons can request unmasking of the treatment allocation. These situations will be documented; but analyses will be performed on the intention-to-treat population.

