### Sample size calculation

In our recent randomized controlled trial, PPCs occurred in 51.7% of patients in the placebo group [11]. Mazo et al. reported incidences of PPCs from 42.1% to 44.9% in high-risk patients (ARISCAT risk score ≥ 45) [4]. Whereas perioperative inhalation of tiotropium reduced the incidence of PPCs by 16% [6], and inhalation of penehyclidine during the first three postoperative days reduced the incidence of PPCs by 12.4% [11]. In the present study, we assume that the incidence of PPCs will be 42.1% in high-risk patients of the placebo group, and prophylactic penehyclidine inhalation will reduce the incidence of PPCs by 10%. The calculated sample size that will provide 80% power to detect a superiority of this difference at a one-sided significance level of 0.025 is 360 patients in each group. Considering a dropout rate of about 20%, we plan to enroll 432 patients in each group. The sample size calculation was performed with PASS 2008 software.

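### Randomisation is stratified by type of surgery, but the primary chi-square test, its confidence interval and the log-rank test ignore the stratum; the cost is small and the remedy is free

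*Protocol article*

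**What the plan says.** On the design, the section on randomisation, blinding and study drug administration states "Randomization will be stratified according to the type of surgery (upper abdominal or noncardiac thoracic surgery". Allocation is 1:1: "Random numbers were generated in a 1:1 ratio using the SAS 9.2 software package".

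On the analysis, the Outcome analysis section states "Primary outcome (the incidence of PPCs within 30 days after surgery) will be compared with χ2 test", followed by "The difference between groups and the 95% confidence interval of the difference will be calculated". For time-to-event outcomes, which would include time to onset of PPCs, it plans Kaplan-Meier estimates and says that "the differences between groups will be tested by the log-rank test". No stratified, Mantel-Haenszel or adjusted version is named for any of these.

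Type of surgery enters the analysis in one place only: "Subgroup analyses will be performed according to the type of the surgery (upper abdominal or thoracic". A subgroup analysis does not bring the stratum into the overall test or the overall interval.

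Table 1 (ARISCAT risk index) lists the surgical incision among the independent predictors of PPCs, with 15 points for upper abdominal and 24 for intrathoracic.

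**The concern.** Stratified 1:1 allocation balances the arms on type of surgery. If the two types carry different PPC risks, the difference between strata then no longer contributes to chance variation in the treatment comparison. The ordinary chi-square variance does not know this and still counts the between-stratum part. The test is therefore somewhat conservative, and the interval for the risk difference somewhat wider than the design warrants. The same reasoning applies to an unstratified log-rank test.

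This is not detail left to a later document. The article names the primary test, and the named test does not match the named randomisation scheme. At stake is some precision on the primary outcome that the design has already secured.

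**Working it through.** **Inputs from the article (Sample size calculation).** Placebo rate: "we assume that the incidence of PPCs will be 42.1% in high-risk patients of the placebo group". Effect: "prophylactic penehyclidine inhalation will reduce the incidence of PPCs by 10" per cent, read as an absolute 10 points, so 32.1% on penehyclidine. A relative 10% reduction would need about 2125 per group, so the article's figure fits only the absolute reading. One-sided alpha is 0.025, power 80%, 360 per group before dropout and 432 enrolled per group.

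**Inputs assumed.** The article gives neither PPC rates by stratum nor the share of each stratum. I take a 50:50 split, the same 10-point effect in both strata, and a gap g between stratum rates of 0 to 30 points around the overall rates.

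**Step 1: the plan's own figure.** With p1 = 0.421, p2 = 0.321 and mean rate 0.371:

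- Pooled formula: n = [1.960 × √(2 × 0.371 × 0.629) + 0.842 × √(0.421 × 0.579 + 0.321 × 0.679)]² / 0.10² = 365.1, so 366.
- Unpooled formula: n = (1.960 + 0.842)² × 0.4617 / 0.10² = 362.4, so 363.
- Power at 360 per group by the pooled test: 79.4%.

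The stated 360 is reproduced closely enough, and it is a calculation for an unstratified comparison.

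**Step 2: variances with and without the stratum.** Per patient in each arm:

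- Unstratified: p1(1 − p1) + p2(1 − p2) = 0.4617.
- Stratified: the average within strata of the same quantity. With equal strata and a constant effect this is 0.4617 − g²/2.
- The null variance used by the test falls by the same amount: 0.4667 becomes 0.4667 − g²/2.

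**Step 3: worked example, 20-point gap, 360 per arm.** Control rates are 32.1% and 52.1%.

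- Stratified variance: 0.4617 − 0.0200 = 0.4417.
- Standard errors: √(0.4617/360) = 0.03581 and √(0.4417/360) = 0.03503.
- 95% half-widths: 7.02 and 6.87 points; ratio 1.022.
- The true sampling standard error under stratified allocation is 0.03503 whichever test is used. The tests differ in the null standard error: √(0.4667/360) = 0.03601 unstratified, √(0.4467/360) = 0.03523 stratified.
- Power, unstratified: Φ[(0.10 − 1.960 × 0.03601)/0.03503] = 80.0%.
- Power, stratified: Φ[(0.10 − 1.960 × 0.03523)/0.03503] = 81.2%.
- Actual one-sided type I error of the unstratified test: Φ(−1.960 × 0.03601/0.03523) = 0.0226.

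**Step 4: range of gaps, 360 per arm, 50:50 split.**

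| Gap (points) | Half-width, unstratified / stratified (points) | Excess width | Power, unstratified / stratified | One-sided type I error, unstratified |
|---|---|---|---|---|
| 0 | 7.02 / 7.02 | 0% | 79.4% / 79.4% | 0.0250 |
| 10 | 7.02 / 6.98 | 0.5% | 79.6% / 79.9% | 0.0244 |
| 20 | 7.02 / 6.87 | 2.2% | 80.0% / 81.2% | 0.0226 |
| 30 | 7.02 / 6.67 | 5.3% | 80.7% / 83.3% | 0.0196 |

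With a 30:70 split the figures are slightly smaller: at a 20-point gap, 1.9% of width and 1.0 power point.

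**Step 5: simulation check.** In 200,000 simulated trials per scenario (360 per arm, 50:50), chi-square against Cochran-Mantel-Haenszel gave power of 79.4% and 79.4% at no gap, 79.6% and 79.8% at 10 points, 79.9% and 81.3% at 20 points, and 80.7% and 83.4% at 30 points. This agrees with the formulas.

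The log-rank part holds in direction only. The article gives no event times or hazards by stratum, so its size cannot be computed.

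**The case against.** The strongest reply is that the harm depends on a quantity the article does not give, and that Table 1 does not settle it for this trial. Every patient must score at least 45. An elective upper abdominal patient aged 51 to 80 with surgery over 3 hours scores 15 + 23 + 3 = 41 and needs a further risk factor to qualify. A thoracic patient reaches 24 + 23 = 47 on incision and duration alone. Selection therefore offsets the 15 against 24 points, and the gap between strata could be small or even reversed. This stands: the loss must be stated conditionally, and large gaps have no support in the article.

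Three stronger readings are tempting, and the article does not support them.

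- A reader might infer that the trial lacks the power to bear the loss. The sample size was itself calculated for an unstratified test, so the loss is relative to a better test and not to the promised 80%. If all 432 per arm are analysed, unstratified power is about 86% even with no gap, and the article keeps dropouts in the intention-to-treat analysis.
- A reader might infer that the primary test is invalid. It is not: the error is conservative at every gap examined.
- A reader might infer that the two types of surgery will be judged by separate significance tests, because no interaction test is mentioned. The article says only that subgroup analyses will be done. How they will be judged is commonly left to an analysis plan.

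The objection does not remove the mismatch itself, nor the fact that stratifying costs nothing even when the strata have equal risk.

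**Conclusion.** The point holds as a minor mismatch between design and analysis. The primary test, its interval and the log-rank test ignore the factor used to stratify randomisation. If PPC risk differs by type of surgery, the primary test is slightly conservative and its interval slightly too wide. For gaps up to 20 points the cost is at most about 1.2 power points and about 2% of interval width, and it is nil if the strata have equal risk. These sizes rest on assumed stratum rates, equal strata, 360 per arm and a constant 10-point effect. The direction needs only a difference in risk between the strata. The validity of the test and the planned power are not in question.

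**What to change.** In the Outcome analysis section, make the primary analysis a Cochran-Mantel-Haenszel test stratified by type of surgery as randomised, and report the Mantel-Haenszel (stratified) risk difference with its 95% confidence interval. For time to onset of PPCs, use a log-rank test stratified by the same factor. Record the change before unblinding, so that the choice between the plain and the stratified test cannot depend on the results.

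The cost is a change of wording. Type of surgery is known for every patient at randomisation, so no new data are needed. No alpha is spent and the sample size need not change. With two large strata nothing is lost if the stratum rates turn out equal, as the zero-gap row of the table shows.

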### Participants

The inclusion criteria are (1) patients of 50 years or over, (2) scheduled to undergo upper abdominal or noncardiac thoracic surgery with expected duration of 2 hours or longer. For those who undergo thoracoscopic or laparoscopic surgery, the expected length of incision must be 5 cm or more, and (3) judged to be at high risk of PPCs according to the ARISCAT risk score (cumulative ARISCAT risk score ≥ 45, see Table 1).

**Table 1 Tab1:** ARISCAT (Canet) risk index

Independent predictors of risk for PPCs		Risk score
Age, years		
≤ 50		0
51–80		3
> 80		16
Preoperative SpO_2_, %		
≥ 96%		0
91–95%		8
≤ 90%		24
Respiratory infection in the last month		
No		0
Yes		17
Preoperative anemia (HbO_2_ ≤ 10 g/dl)		
No		0
Yes		11
Surgical incision		
Peripheral		0
Upper abdominal		15
Intrathoracic		24
Duration of surgery, hours		
≤ 2		0
2–3		16
> 3		23
Emergency procedure		
No		0
Yes		8
Risk class	Number of points in risk score	Pulmonary complications rates
Low risk	<26 points	1.6%
Intermediate risk	26–44 points	13.3%
High risk	≥45 points	42.1%

*PPC* postoperative pulmonary complications

Patients who meet any of the following criteria will be excluded: (1) American Society of Anesthesiologists (ASA) physical classification ≥ IV or the expected survival duration ≤ 24 hours; (2) preoperative history of moderate-to-severe symptomatic prostatic hypertrophy or narrow-angle glaucoma; (3) history of myocardial infarction, severe heart dysfunction (New York Heart Association functional classification ≥ 3) or tachyarrhythmia within 1 year; (4) inhalation of β2-receptor activator, M-receptor blockers and/or glucocorticoids within 1 month before surgery; (5) severe renal dysfunction (requirement of renal replacement therapy) or severe hepatic dysfunction (Child-Pugh grade C); (6) history of acute stroke within 3 months before surgery; (7) unable to cooperate in the inhalational therapy; (8) participation in other clinical trial during the last month or within the six half-life periods of the study drug used in the last trial; or (9) refuse to participate in the study.

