Criteria of dropout include the following: (1) consent withdrawn by the participants themselves (at least one dose of study drug has been administered); (2) loss to follow‐up; (3) ordered to exit by the investigators or attending physicians (poor compliance, occurrence of severe complications, or occurrence of severe adverse events); (4) prophylactic use of any prohibited drugs (anticholinergics or any medications other than the study drugs) from study recruitment to postoperative day 2; or (5) blindness unmasked. For dropout cases, detailed reasons will be recorded in the case report forms (CRFs). The primary therapeutic effects recorded the last time will be regarded as the final results. These cases will be included in the intention-to-treat analysis but excluded from the per protocol analysis.

Criteria of rejection include the following: (1) consent withdrawn by the participants themselves (study drug is not administered); (2) no study record; or (3) surgery delayed or canceled, unable to assess the occurrence of PPCs. For rejected cases, detailed reasons will be recorded in the CRFs. These cases will be excluded from analysis of therapeutic effects.

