#### Primary outcome

The primary outcome is the incidence of PPCs within 30 days after surgery. In the present study, PPCs are generally defined as any condition that affects the respiratory tract system and may adversely influence patients’ outcome [1]. The diagnostic criteria of each individual PPC are listed in Table 2 [3]. We adopt the Clavien-Dindo Classification to categorize PPCs into five major groups [12, 13], and PPCs of grade II or above will be used to calculate the incidence of PPCs (Additional file 3). If a PPC occurs during the follow-up period, the date of earliest diagnosis and the evidences according to which the diagnosis is made will be documented.

**Table 2 Tab2:** Definitions of PPCs

Complications	Definition
Respiratory infections	Receiving antibiotics for a suspected respiratory infection and met at least one of the following criteria: new or changed sputum, new or changed lung opacities, fever, leukocyte count >12 × 10^9^/L
Respiratory failure	PaO_2_ < 60 mmHg on room air, a ratio of PaO_2_ to inspired oxygen fraction < 300, or arterial oxyhemoglobin saturation measured with pulse oximetry < 90% and requiring oxygen therapy
Pleural effusion	Chest X-ray demonstrating blunting of the costophrenic angle, loss of the sharp silhouette of the ipsilateral hemidiaphragm in upright position, evidence of displacement of adjacent anatomical structures, or (in supine position) a hazy opacity in one hemithorax with preserved vascular shadows
Atelectasis	Lung opacification with a shift of the mediastinum, hilum, or hemidiaphragm toward the affected area, and compensatory overinflation in the adjacent nonatelectatic lung
Pneumothorax	Air in the pleural space with no vascular bed surrounding the visceral pleura
Bronchospasm	Newly detected expiratory wheezing treated with bronchodilators
Aspiration pneumonitis	Acute lung injury after inhalation of regurgitated intragastric contents

*PPCs* postoperative pulmonary complications

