#### Secondary outcomes

Secondary outcomes include the time to onset of PPCs (from end of surgery to first diagnosis of PPCs), the number of PPCs (indicate the number of diagnosed individual PPCs), the incidence of postoperative extrapulmonary complications, the length of stay (LOS) in hospital after surgery, and the 30-day all-cause mortality. Postoperative extrapulmonary complications are defined as complications other than PPCs that occur within 30 days after surgery and require therapeutic intervention. For each diagnosed extrapulmonary complications, the date of earliest diagnosis and the evidences according to which the diagnosis is made will also be documented.

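### Death before a PPC is not addressed: the fixed methods count it as a non-event in the primary test and censor it in the time-to-onset curve, a small gap that one sensitivity analysis closes

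*Protocol article*

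**What the plan says.** All places are in the protocol article.

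- **Primary outcome:** "The primary outcome is the incidence of PPCs within 30 days after surgery. In the present study" the event is then narrowed by severity: "PPCs of grade II or above will be used to calculate the incidence of PPCs". Table 2 lists seven respiratory conditions. Death is not one of them.
- **General principles:** all subjects are analysed in the group to which they were assigned.
- **Outcome analysis, primary:** "Primary outcome (the incidence of PPCs within 30 days after surgery) will be compared with" a chi-squared test, with the difference and its 95% confidence interval.
- **Secondary outcomes:** these include "the time to onset of PPCs (from end of surgery to first diagnosis of PPCs", so death does not end the interval. Thirty-day all-cause mortality is a separate secondary outcome.
- **Outcome analysis, secondary:** "time-to-event results will be analyzed using the Kaplan-Meier estimator, and the differences between groups will be tested by the log-rank test". No censoring or competing-event rule is given.
- **Participants, dropout criteria:** death is not listed by name, but exit ordered because of severe complications or severe adverse events is. For dropouts, "The primary therapeutic effects recorded the last time will be regarded as the final results", and they stay in the intention-to-treat analysis.

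The article gives no expected mortality and does not say how a death before a PPC is handled.

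**The concern.** A patient who has died can no longer develop a PPC, so death without a PPC is a competing event. The patients are at least 50 years old, have an ARISCAT score of at least 45 and undergo major thoracic or upper abdominal surgery, so some such deaths can be expected.

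For the binary outcome, both routes through the text end in the same score. A patient who dies without a PPC and is not a dropout is in the denominator without an event. If the patient is treated as a dropout, the last recorded result, no PPC, becomes final. An arm with more PPC-free deaths would then show fewer PPCs for a reason that is not prevention.

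For time to onset, an event that ends only at PPC diagnosis leaves Kaplan-Meier no option but to censor at death. One minus Kaplan-Meier then estimates PPC incidence as if nobody could die first, which is not the incidence that patients experience.

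Reporting mortality separately would reveal an imbalance. It would not show how far the imbalance had moved the PPC difference.

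**Working it through.** **Inputs from Sample size calculation:** placebo PPC rate 42.1%; reduction 10 points (to 32.1%); one-sided 0.025; 80% power; 360 per group, 432 enrolled per group.
**Assumed:** all death rates. None is given, so ranges are shown.

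**1. The plan's own figure.** Unpooled: n = (1.96 + 0.842)² × (0.421×0.579 + 0.321×0.679) / 0.10² = 363 per group. The pooled variant gives 366. Both are within 2% of 360, so the figure reproduces. Power at 360 per group is 79.4%. The sample size does not depend on this point.

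**2. Equal PPC-free deaths in both arms.** Let a share q die before any PPC, independently of PPC risk. The observed rates are 0.421(1−q) and 0.321(1−q), so the difference is 10.0(1−q) points.

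| q | Difference (points) | Power at 360 per group |
|---|---|---|
| 0 | 10.0 | 79.4% |
| 1% | 9.9 | 78.8% |
| 2% | 9.8 | 78.2% |
| 5% | 9.5 | 76.2% |

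Balanced deaths dilute the effect slightly. They do not create a benefit.

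**3. Excess PPC-free deaths on penehyclidine, no true effect on PPC.** Spurious difference = excess × f, where f is the share of those patients who would have had a PPC. With 432 per group, SE = √(2×0.421×0.579/432) = 3.36 points. The one-sided error is Φ(spurious difference/SE − 1.96).

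| Excess (points) | Bias, f = 0.421 | One-sided error | Bias, f = 1 | One-sided error |
|---|---|---|---|---|
| 1 | 0.4 | 3.3% | 1.0 | 4.8% |
| 2 | 0.8 | 4.4% | 2.0 | about 8.6% |
| 3 | 1.3 | 5.7% | 3.0 | about 14.3% |

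An observed difference of 1.96 × 3.36 = 6.6 points is needed for significance. To produce it from deaths alone would take an excess of 6.6 points at f = 1, or 6.6/0.421 ≈ 15.6 points at average risk.

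**4. Kaplan-Meier curve.** Take constant hazards over 30 days, death independent of PPC. The cumulative PPC hazard is Λ = −ln(0.579) = 0.5465, and the cumulative death hazard is M = −ln(1−d). One minus Kaplan-Meier estimates 42.1%. The true cumulative incidence is Λ/(Λ+M) × [1 − exp(−(Λ+M))].

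- d = 1%: M = 0.0101, incidence 41.9%, overstated by 0.2 points.
- d = 2%: M = 0.0202, incidence 41.7%, overstated by 0.4 points.
- d = 3%: M = 0.0305, incidence 41.5%, overstated by 0.6 points.

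**5. Tests for time to onset.** Simulation with 432 per arm, 20,000 runs, no effect on the PPC hazard and independent deaths. The table gives one-sided rejection in the drug's favour (nominal 2.5%).

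| Deaths, placebo vs active | Chi-squared | Log-rank | Gray's test |
|---|---|---|---|
| 1% vs 1% | 2.4% | 2.4% | 2.4% |
| 1% vs 3% | 3.2% | 2.5% | 3.2% |
| 1% vs 5% | 4.1% | 2.5% | 3.9% |

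Log-rank removes the dead from the risk set and stays at its nominal level. Gray's test keeps them in as event-free and is exposed in the same way as the chi-squared test.

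**6. Does the sensitivity analysis show the problem?** In step 3 with a 2-point excess at f = 0.421, PPC alone favours the drug by 0.84 points. PPC or death goes the other way by 2 − 0.84 = 1.16 points. At f = 1 the composite difference is zero. In both cases the false benefit disappears.

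**The case against.** **The document is silent, and a rule may sit elsewhere.** This is fair. Neither scoring as PPC-free nor censoring at death is a written rule, and an analysis plan or full protocol may deal with it. But the article does fix the event definitions, the intention-to-treat population and the methods, and those lead to this handling unless another document changes it. The point concerns the consequence of fixed methods, not only a missing detail.

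**The effect is small and needs an imbalance.** This stands. The bias at average risk is 0.4 to 1.3 points against a 10-point target, and only under an assumed excess. ASA class IV or above and expected survival of 24 hours or less are excluded. Table 2 is also broad enough that many deteriorating patients would probably meet a PPC definition before death. Separate reporting of mortality would expose a large imbalance.

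**Stronger readings that a reader might infer, and that the documents do not support:**

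- *Time to onset also moves in the drug's favour.* It does not when deaths are independent of PPC risk: log-rank held at about 2.5%. If frail patients are prone to both, censoring becomes informative, but nothing in the document gives a size for that.
- *The cardiac exclusions ("history of myocardial infarction, severe heart dysfunction" among them) show that a lethal drug effect was suspected.* They show caution in selection and also remove patients at risk of cardiac death.
- *The abstract's link between PPCs and mortality supports the concern.* Deaths that follow a qualifying PPC already count as events. The link says nothing about PPC-free deaths.

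**Conclusion.** The point holds as a minor one. As defined, the primary comparison counts death before a PPC as a non-event. It is therefore biased towards penehyclidine if such deaths are more frequent on that arm, and against it if they are less frequent. For an assumed excess of 1 to 3 points the bias is about 0.4 to 1.3 points at average PPC risk and 1 to 3 points at most. It could matter only for a result near the significance boundary. With balanced deaths the effect is slightly diluted, and with none there is no bias.

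For time to onset, the log-rank test is a valid comparison of PPC hazards provided deaths are independent of PPC risk. Only the displayed incidence is off: one minus Kaplan-Meier is too high by about 0.2 to 0.6 points at 1 to 3% deaths.

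All of these sizes rest on assumed death rates. The document neither shows nor implies that penehyclidine raises mortality.

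**What to change.** 1. Keep the primary outcome and the chi-squared test. State that a patient who dies without a PPC counts as having no PPC in the primary analysis.
2. Prespecify one sensitivity analysis with the event PPC of grade II or above, or death from any cause, within 30 days, using the same test and confidence interval.
3. Tabulate deaths without a PPC by arm.
4. For time to onset, keep the log-rank test, described as a cause-specific comparison with deaths censored. Replace one minus Kaplan-Meier by cumulative incidence curves with death as a competing event.
5. Do not replace log-rank by Gray's test, which would bring into the time-to-onset comparison the weakness that log-rank avoids.

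The cost is a few lines in the analysis section, settled before unblinding, and one additional sensitivity result to report. Thirty-day mortality and the date of first PPC diagnosis are already to be recorded. The curves also need the date of death, which the 30-day follow-up should supply. No further patients are needed.
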